### Participant timeline {13}

The schedule of enrolment, interventions, and assessments is outlined below in Fig. 3.

**Fig. 3 Fig3:**
[figure not shown]
Schedule of enrolment, interventions, and assessments

#### Sample size {14}

The primary outcome of this study will be the QoR-15 score at 24 h postoperatively. This score rates 15 subjective, patient-reported parameters about their recovery on a scale of 0–10. Therefore, the minimum possible score is 0, and the maximum possible score is 150. The established minimum clinically important difference in QoR-15 is 6.0 [14], and the mean SD of QoR-15 scores after major surgery is in the order of 8–16. Taking an SD of 8, and assuming type I error = 0.05 and type II error = 0.2 (80% power to detect this difference), then *n* = 28 patients will be required in each group. To accommodate for participants who may withdraw from the study, we will aim to recruit *n* = 30 patients to each study arm, i.e. *n* = 60 in total.

#### Recruitment {15}

Members of the anaesthetic and surgical research team from each clinical site will engage in the recruitment process.

### Assignment of interventions: allocation

#### Sequence generation {16a}

Participants will be randomised to either PIB vs CI group by using an online computer-generated block randomisation (https://www.sealedenvelope.com). Block randomisation will occur in groups of 6 to ensure each arm of the study has an even number of participants. The trial investigators will not have access to the randomisation key/seed until completion of the study.

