### Trial design {8}

We outline a research protocol for a double-blind, randomised controlled, superiority trial. Patients who enrol to this clinical trial will be randomly and equally (1:1) allocated into one of two intervention groups: programmed intermittent bolus (PIB) regime of local anaesthetic vs a continuous infusion (CI) of local anaesthetic via an ultrasound-guided erector spinae plane block catheter. Both groups will receive the same standardised pain relief protocol both during and after their surgery. Figure 1 illustrates the study flow chart. Recruitment commenced on June 2022, and it is expected to take between 9 and 12 months to complete.

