## Methods: participants, interventions, and outcomes

### Study setting {9}

Ethical approval (Institutional Review Board; reference number 1/378/2292) has been granted for Mater Misericordiae University Hospital (MMUH), Dublin, Ireland, and recruitment has begun. In addition, we are currently seeking ethical approval for a second clinical site (St. James’s Hospital, Dublin, Ireland).

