### Who will take informed consent? {26a}

Potential participants for this trial will be identified by a member of the surgical, anaesthetic or research team. These patient’s electronic medical records will be analysed by a member of the research team to determine if they are suitable candidates for this trial, i.e. if they meet the inclusion criteria and have no reason for exclusion.

Suitable patients will be approached the evening before surgery where possible. Alternatively, patients will be approached on the ward on the morning of surgery and their suitability to participate in the trial will be confirmed. The purpose of the trial including benefits and risks, and method of follow up will be explained to patients. A comprehensive and instructive information leaflet will be given to each patient, and they will be provided an adequate amount of time to study it (minimum 10 min). Patients will be informed that their participation in the study is entirely voluntary and they will have the opportunity to withdraw from the study at any time, and this will not affect the quality of care they receive. Finally, a member of the research team will obtain informed written consent from the participant.

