### Assignment of interventions: blinding

#### Who will be blinded {17a}

This study will be a double-blinded clinical trial. Patients will be blinded to the study because they will receive the intervention after they have been put under general anaesthesia. Members of the research team involved in data collection and analysis will be masked to group allocation. The treating anaesthesiologist and surgeon will not be blinded.

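### One fixed, published block size of 6, with unblinded clinicians whose teams also recruit, would let a fully informed observer deduce up to a quarter of allocations in advance

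*Protocol article*

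**What the plan says.** All references are to the protocol article.

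- **Block size.** Sequence generation {16a}: "Block randomisation will occur in groups of 6 to ensure each arm of the study has an even number of participants". No second size and no stratification factor is mentioned.
- **Ratio and total.** Under Trial design {8}, patients are "randomly and equally (1:1) allocated into one of two intervention groups". Under Sample size {14}, "we will aim to recruit *n* = 30 patients to each study arm, i.e. *n* = 60 in total".
- **Who knows allocations.** Under Implementation {16c}, the treating anaesthesiologist opens the envelope, after consent is confirmed and after induction. Who will be blinded {17a} adds: "The treating anaesthesiologist and surgeon will not be blinded".
- **Who finds patients.** Who will take informed consent? {26a}: "Potential participants for this trial will be identified by a member of the surgical, anaesthetic or research team". Recruitment {15} gives the recruiting role to anaesthetic and surgical research team members at each site.
- **Safeguards.** An independent third party performs the randomisation, investigators have no key or seed until the study ends, and the envelopes are opaque, sealed and sequentially numbered ({16a}, {16b}).
- **Timing.** Trial status says that recruitment began on 2 June 2022 and was expected to finish by July 2023, so the article describes a trial that was already enrolling.

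**The concern.** Concealment needs two things: nobody can see the next allocation, and nobody can work it out. The article provides well for the first. The second is weakened by a single block size that is in print, because every block must then hold exactly three patients per arm. Once one arm has used its three places, the rest of the block is known.

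Clinicians who learn each allocation belong to the same teams that put candidates forward. Patients are approached the evening before or the morning of surgery, when the next allocation may already be deducible. Opening the envelope only after induction does not help against that.

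At stake is selection bias, meaning that a fitter or frailer patient is put forward according to the arm that is due. The features of this trial would make such bias hard to detect or correct. The sample is small and the primary outcome is patient-reported. The Discussion says that no preoperative QoR-15 is taken, so there is no baseline on the outcome's own scale. The comparison in {20a} is an unadjusted t test or Mann-Whitney test.

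**Working it through.** **Inputs.** Block size 6 ({16a}); 1:1 ratio ({8}), hence 3 and 3 per block; 60 patients ({14}), hence 60 / 6 = 10 blocks. The article gives no predictability figure to reproduce. Its sample size does reproduce: 2 × [8 × (1.960 + 0.842) / 6]² = 27.9, so 28 per arm (two-sided normal approximation), raised to 30.

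**Certain allocations, full observer.** This observer knows the block size, the block start and every earlier allocation in the block. A 3:3 block has C(6,3) = 20 equally likely orderings. Counting the places left once one arm is full:

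| Places certain at the end of the block | Share of blocks |
|---|---|
| exactly 1 | 60% |
| exactly 2 | 30% |
| 3 | 10% |

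Expected number = 0.6 × 1 + 0.3 × 2 + 0.1 × 3 = 1.5. The closed form for a block of 2m, 2m/(m + 1), gives 6/4 = 1.5. So 1.5 / 6 = 25%, and 10 × 1.5 = 15 of 60. The sixth place is always certain, and the last two or more are certain in 40% of blocks.

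**Best guess, full observer.** Always guessing the arm that is behind gives m + 2^(2m−1)/C(2m,m) − 0.5 = 3 + 32/20 − 0.5 = 4.1 correct of 6, or 68.3%, against 50% by chance.

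**Partial observer (assumption).** If each allocation in the block were visible only with some probability, enumeration gives about 11% certain at 75% visibility and about 3% at 50%.

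**Varying block sizes.** I simulated 2,000 lists of 60. The observer sees every allocation and knows the set of sizes, but not their order.

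| Block sizes | Certain | Best guess correct |
|---|---|---|
| 6 only | 25.0% | 68.3% |
| 4, 6 | 5.5% | 69.1% |
| 4, 6, 8 | 2.2% | 67.8% |

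Over 60 patients, 25% is 15 certain allocations, 5.5% is 3.3 and 2.2% is 1.3. The gain is in certainty and not in guessing.

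**What it could do to the result (illustration, assumed).** Suppose that selection acts only on the certain quarter. Those patients have an expected QoR-15 that is d points higher in the favoured arm and d points lower in the other. The bias in the difference is 0.25d + 0.25d = 0.5d. For d from 2 to 8 that is 1 to 4 points, against the minimum important difference of 6.0 used in {14}. The article gives no basis for any value of d, and d may be zero.

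**The case against.** The strongest reply is that nobody in the article is shown to be the full observer. Each treating anaesthesiologist opens the envelope for his or her own case, and nothing says that allocations are pooled. A research team member checks eligibility from records and takes consent. Those who collect and analyse data are masked. This stands: 25% is a ceiling, and the text shows overlapping teams rather than one person in both roles. It does not remove the point, because knowledge of allocations and identification of candidates lie in the same teams, and at a single active site keeping track is feasible.

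The safeguards are also real. They confine the risk to deduction from earlier allocations, but they leave that route open.

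A third reply is that varied blocks barely change best-guess accuracy. That is correct and limits the benefit: a determined guesser keeps some advantage, but is almost never sure.

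A reader might also infer that one list, not split by site, serves two hospitals and could unbalance the arms by hospital. The article does not support this. It never says whether lists or envelope series are shared or separate, such detail commonly sits in the full protocol, and for the second hospital it says only "we are currently seeking ethical approval for a second clinical site". The inference also pulls against the 25%. If one list were shared and a site saw only half of the allocations, about 3% would be certain there.

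**Conclusion.** The point holds in a limited form. A single block size of 6, public during enrolment, combined with unblinded clinicians from recruiting teams, leaves up to 25% of allocations (at most 15 of 60) deducible with certainty. That figure assumes an observer who knows the block start and every earlier allocation; with less knowledge it falls quickly.

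A reader might infer that a quarter of allocations are in fact known in advance, or that selection has occurred. The article supports neither. This is an avoidable weakness in concealment, of moderate weight, and worth correcting because the correction is cheap. Nothing is established about site.

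**What to change.** For the remaining allocations, have the independent third party issue a new list with block sizes varying at random, for example 4, 6 and 8. Neither the sizes nor their order should be disclosed to investigators or recruiting staff. The working protocol should say only that varying block sizes are used.

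Costs:
- **Envelopes.** A new list from the same kind of tool and a new envelope series.
- **Balance.** If enrolment stops inside a block of 8, the arms can differ by at most 4, that is 32:28. The variance of the difference then rises from 2/30 = 0.0667 to 1/32 + 1/28 = 0.0670 (in units of SD²), about 0.4%. This assumes that the switch is made when a block of six is complete.
- **Approval.** The amendment section {25} treats changes to study design as substantial, so ethics approval may be needed.
- **Timing.** The benefit shrinks with the number of patients left. If enrolment is complete, the fixed block size should be reported as a limitation instead.

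One question for the investigators: if the second hospital opens, will it have its own list and envelope series, and will the analysis account for site? The article refers to more than one site in {15}, {5d} and {23} but leaves this open.

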#### Concealment mechanism {16b}

The participant study number and group allocation will be typed onto separate pages and concealed in sequentially numbered, opaque, sealed envelopes. The randomisation process will be performed by an independent third party who is not involved in the conduction of this trial.

#### Implementation {16c}

After confirming that informed consent for participation in this trial has been signed by the participant, a sealed envelope will be opened by the treating anaesthesiologist to reveal the group allocation. This process will occur *after* induction of general anaesthesia to ensure the patient is blinded to the study intervention.

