#### Intervention description {11a}

Eligible study participants will receive an ultrasound-guided ESP block post induction of general anaesthesia and prior to commencement of surgery. Blocks will be performed under full asepsis with patients in the lateral decubitus position. Initial bolus of the ESP block will be the same in all patients: Twenty millilitres of 0.25% levobupivacaine will be injected at a level corresponding to the mid-point of the range of surgical dermatomes likely to be affected by the surgery. After administration of the bolus dose, an epidural catheter will be advanced 3–5 cm into the erector spinae space. Typically, ESP block and catheter insertion will be administered at T4 level. The ESP block will be performed as follows.

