First, the approximate midpoint of the intended surgical incision will be identified. The ultrasound transducer (SonoSite HFL 50x, SonoSite Inc.) will then be placed in a longitudinal orientation approximately to 2–3 cm lateral to the midline, to identify the hyperechoic line of the transverse process with its associated acoustic shadow. After identification of trapezius, rhomboid major and erector spinae muscle groups superficial to the transverse process, an 18G Tuohy epidural needle (Ultraplex; B. Braun, Hessen, Germany) will be advanced in a cranio-caudal direction. The needle tip will be advanced until it is in the interfascial plane deep to the erector spinae muscle group and superficial to the transverse process. Once in position, 20 ml 0.25% levobupivacaine will be injected under ultrasound guidance. Correct needle tip position will be confirmed by the presence of linear spread between the transverse process and the erector spinae muscle group. After administration of a bolus dose, a 20G polyether epidural catheter (Ultraplex 360 cannula; B. Braun, Hessen, Germany; 50e80 mm) will be advanced through the Tuohy needle and into the ESP space. The catheter will be adjusted so that approximately 3–5 cm of the catheter will be in the ESP space. The catheter will then be secured in this position. Because patients will be under general anaesthesia during the block performance, no formal dermatomal sensory testing of block efficacy will be performed at this time. Surgery will begin once the block is completed. There will be no further intervention to the routine conduct of surgery and anaesthesia after this point. Blocks will be performed by anaesthesiologist with subspeciality training in regional anaesthesia. Two hours post administration of the ESP bolus dose, the ESP catheter will be connected and commenced with either the PIB or CI regimen (randomised process).

The PIB patients will receive levobupivacaine 0.125% programmed bolus 20 ml 2 hourly. The CI group will receive continuous infusion levobupivacaine 0.125% at 10 ml.h^−1^. Therefore, both arms of the study will receive 25mg levobupivacaine every 2 h.

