#### Relevant concomitant care permitted or prohibited during the trial {11d}

All study participants will undergo general anaesthesia (GA) as per standard care for MITS. Induction of GA will be conducted or supervised by a consultant anaesthesiologist. Induction of GA will be achieved intravenous administration of fentanyl, propofol, and a neuromuscular blockade agent at the discretion of the anaesthesiologist.

Airway management will be at the discretion of the treating anaesthesiologist. Ventilation strategy, choice of intraoperative monitoring, and vascular access will also be at the discretion of the treating anaesthesiologist. The haemodynamic goal will be to maintain systolic blood pressure within 20% of the patient’s baseline. Persistent intraoperative elevations above this point will trigger the administration of intravenous opioids. The dosage and timing of this will be at the discretion of the treating anaesthesiologist. Intravenous (IV) paracetamol and an IV non-steroidal anti-inflammatory drug will be delivered intraoperatively where clinically appropriate and at the discretion of the treating anaesthesiologist.

A concomitant care plan for perioperative analgesia and anti-emetics will be standardised for the pre-surgical, intra-operative, PACU, and post-operative period. This is outlined in Fig. 2.

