We acknowledge some limitations to this protocol including the fact that the treating anaesthesiologist will not be blinded to the group allocation as they will be required to perform the block. However, the primary will be measured 24 h postoperatively by researchers blinded to the group allocation, thus maintaining blinding of data. We acknowledge that for some patients having MITS their recovery will continue beyond 48 h postop; however, the acute postoperative pain following MITS is diminished by day 3, and many of our patients will be discharged home at this stage. Length of stay and postoperative complications will continue to be observed until patient discharge. ESP catheters will be placed under general anaesthesia; therefore, formal dermatomal assessment of block function will not be possible, and we will not be formally testing block effectiveness. However, the practice of placing these catheters under ultrasound guidance after induction of general anaesthesia is in line with common clinical practice, and therefore, our findings should still be applicable to widespread clinical practice. Assessment of preoperative QoR-15 will not be undertaken in this study. Therefore, we will not have a baseline from which to compare postoperative QoR-15 scores. Nonetheless, QoR-15 was specifically intended for postoperative use, and we will apply this scoring tool equally to both randomised groups. Furthermore, the accuracy of QoR-15 in the immediate pre-operative period has been debated [24]. By focusing on patient-centred outcomes in our trial design, we hope to explicate whether the use of programmed intermittent regimes of delivery of levobupivacaine to the erector spinae plane will result in an improved quality of recovery compared with continuous infusion.

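### The treating anaesthesiologist may learn the allocation from induction onwards, although nothing depends on it until the catheter is connected 2 h after the block

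*Protocol article*

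**What the plan says.** Implementation {16c} sets the moment of allocation: once consent has been confirmed, "a sealed envelope will be opened by the treating anaesthesiologist to reveal the group allocation". This is timed after "induction of general anaesthesia to ensure the patient is blinded to the study intervention". No later limit is given, and the step is not tied to completion of the block or the catheter.

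Who will be blinded {17a} states: "The treating anaesthesiologist and surgeon will not be blinded". The Discussion lists this as a limitation and gives the reason: "the treating anaesthesiologist will not be blinded to the group allocation as they will be required to perform the block".

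Intervention description {11a} places the block after induction and before surgery. It states that "Initial bolus of the ESP block will be the same in all patients" and describes a single needle and catheter technique for everyone. The arms separate later: "Two hours post administration of the ESP bolus dose, the ESP catheter will be connected and commenced with either the PIB or CI regimen".

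The section on concomitant care {11d} says of intraoperative opioid: "The dosage and timing of this will be at the discretion of the treating anaesthesiologist". Intravenous paracetamol and a non-steroidal anti-inflammatory drug "will be delivered intraoperatively where clinically appropriate and at the discretion of the treating anaesthesiologist".

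Section {11b} counts failure to place the catheter among the reasons for discontinuing the study protocol.

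**The concern.** The trial is described as double-blind, and the one clinician who directs intraoperative analgesia is unblinded for a reason that the intervention section contradicts. Performing a block that is identical in both arms does not require knowing the arm.

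What is at stake is performance bias. Intraoperative analgesia can carry over into early pain scores in recovery, time to the first intravenous opioid, time in recovery and nausea and vomiting, all of which are secondary outcomes, and possibly into the 24 h QoR-15. Intraoperative haemodynamic change is itself recorded as an adverse event, and a persistent rise in blood pressure triggers the discretionary opioid. Masking the data collectors protects the measurement of outcomes. It does not protect care given by someone who knows the arm.

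A second consequence is that allocation can precede a step that may fail. A patient in whom the catheter cannot be placed may already belong to an arm.

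**Working it through.** The plan gives no figure on this point, so the check is to put the steps in order and ask at each one whether the allocation is needed.

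1. **Induction of anaesthesia.** The same in both arms; allocation not needed. From here on {16c} allows the envelope to be opened.
2. **Block and initial bolus, before surgery.** {11a} gives one volume and concentration for all patients. Allocation not needed.
3. **Catheter placement.** {11a} describes one technique. Allocation not needed. {11b} allows for failure at this step.
4. **Surgery up to 2 h after the bolus.** No study regimen is running. {11d} leaves opioid dose and timing, paracetamol and the anti-inflammatory drug to the treating anaesthesiologist. Allocation not needed.
5. **Catheter connection, 2 h after the bolus.** The pump must be set to one regimen or the other. Allocation is needed here and for the set-up just before it.

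**Length of needless knowledge.** Let T be the time of the bolus. The arms first differ at T + 2 h. If the envelope is opened at or before T, the interval is (T + 2 h) − T = 2 h or longer. If it is opened d hours after T, with d below 2, the interval is 2 − d hours. {16c} does not fix d. The Discussion, by linking unblinding to the performance of the block, suggests opening at or before T, but this is an inference.

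**The stated purpose of the timing.** {16c} times the opening after induction to keep the patient blinded. That purpose sets an earliest point, not a reason for early opening. Opening later, where the patient can neither see nor hear it, serves it equally.

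**Failed catheter.** If the envelope is opened before step 3, a failure at step 3 occurs after allocation. If it is opened after step 3, that patient is never allocated.

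**The case against.** Several counter-arguments have weight.

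- {16c} says only that opening follows induction. That the catheter is placed by someone who knows the arm is inferred from the Discussion. This stands: the text permits early opening but does not prescribe it.
- Someone must know the arm to set the pump. The 2 h point may fall during surgery, in which case the remaining intraoperative care may be unblinded anyway, or after it, when the patient may be awake. Both stand. They limit what later opening achieves and require that it be done away from the patient.
- Discretion is narrower than it may seem. Intraoperative opioid is tied to a blood-pressure trigger, and {11d} refers to a standardised analgesia plan in Fig. 2, which is not shown. This stands in part, since the text still leaves opioid dose and timing open.
- The arms receive the same drug at the same total dose per 2 h, the primary outcome is collected at 24 h by masked researchers, and the unblinding is openly declared. These points make a large bias less likely. They do not make the early disclosure necessary.

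A reader might go further and infer that failed catheters are post-randomisation losses that erode power, because recruiting 30 per arm against a requirement of 28 leaves only 30 − 28 = 2 spare patients (2/30 = 6.7%). The document does not support this. {11b} lists catheter failure as a reason to discontinue the study protocol, not to leave the analysis. The 24 h questionnaire could still be collected. No failure rate is given, and nothing suggests that failures would differ between arms.

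A reader might also infer that allocation leaks to recovery staff at handover, or that concealment before enrolment is compromised. The document does not say that the arm is passed on at handover, and the sealed-envelope procedure prepared by an independent third party is unaffected.

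**Conclusion.** The point holds as a modest and avoidable design weakness. The reason given in the Discussion for unblinding the anaesthesiologist is contradicted by {11a}, and {16c} allows the arm to be known before anyone needs it, while discretionary analgesic decisions are being made. The needless interval is 2 h or more if the envelope is opened by the time of the bolus, and shorter if it is opened later.

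The effect on outcomes cannot be quantified from the document in either size or direction. Catheter failure after allocation is possible, but its frequency and its consequence for the analysis are not stated, so no loss of patients or power is claimed.

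The conclusion rests on two readings: that {16c} permits opening before the block, which nothing in the text prevents, and that Fig. 2 does not remove the discretion that {11d} expressly leaves.

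**What to change.** Amend {16c} so that the envelope is opened only after catheter placement has been confirmed, and as late as practicable before the pump is set up for connection at 2 h. It should be opened out of the patient's sight and hearing. Where existing staffing allows, the person who opens it should be neither directing intraoperative analgesia nor collecting outcomes.

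Reword the limitation in the Discussion, without deleting it, to say that treating staff are unblinded from pump connection because the regimen must be set, not because the block must be performed. Align {17a} with that wording.

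No treatment, dose or sample size changes. The cost is a short amendment and having the envelope and pump set-up at hand in theatre or recovery at about 2 h. If surgery runs past 2 h, the remaining intraoperative care may still be unblinded, and the revised text should say so.
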